#### Protection against cardiopulmonary risk

During interventions, a team member monitors cardiopulmonary function to ensure safety and comfort. If excessive discomfort or pain is reported, the intervention ends. In case of medical issues that may arise during our interventions, such as symptoms of autonomic dysreflexia (AD), rapid change in HR or systolic BP (SBP), diaphoresis, severe headache, or dizziness, participants will be withdrawn from the experiment and provided skilled care from the research clinicians. The emergency medical team at the clinical sites are notified promptly. Return to the study requires medical clearance.

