#### Protection against low oxygen risks

Moderate reduction in inspired oxygen can cause a lightheaded sensation, dizziness, reduced vision, and euphoria. The research team monitors SpO_2_, HR, and BP before, during, and after the breathing intervention to ensure that administered oxygen levels do not induce cardiopulmonary stress on participants. The breathing system automatically delivers normal room air to participants if their SpO_2_ level falls below 75%. Supplemental oxygen will be available for participants if needed. If participants report signs of a lightheaded sensation, dizziness, reduced vision, and euphoria, the experiment will be stopped, administration of room air or supplemental oxygen will be provided, and a physical therapist and/or physician will reassess the participant.

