#### Blood pressure

We will define a systemic hypertensive event as a systolic pressure exceeding 140 mm Hg and/or diastolic pressure exceeding 90 mm Hg.^46^ For each participant, we specifically record the hypertension incident rate, that is, the number of hypertensive events divided by units of person-measures (the total number of BP measurements), which accounts for the total number of chances for detecting a hypertensive event and for measurements not made because of dropout or a disqualifying adverse event.^47^

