#### Autonomic dysreflexia incidence rate

AD incidence rate is the number of AD events divided by the total person-time (number of study days completed by each participant) to account for the total number of chances for detecting AD for days not measured because of dropout or a disqualifying adverse event.^47^ An AD event will constitute a participant having a SBP increase from baseline of 20 mm Hg not associated with exercise or SBP >150 mm Hg with complaints of headache, diaphoresis, and/or blurred vision and will be diagnosed by our study team clinicians (physicians and physical therapists).

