#### Cognitive ability

We will assess cognitive function after the last walking practice session and after the last intervention session (T_0_, T_2_; Fig. 3).^48^ The California Verbal Learning Test, Third Edition (CVLT3) brief form will quantify verbal learning and memory.^49^ We also assess executive function with the Oral Trail Making Test (O-TMT).^50^ These tests examine the areas of cognitive ability most likely to be affected by an excessive dose of low oxygen, such as during severe sleep apnea.^51^

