To minimize biases and errors in data collection, a designated lead physical therapist, blinded to study interventions, ensures participant adherence to the protocol and consistent scoring among therapists by regularly checking all assessment logs for adherence to standard clinical procedures. Non-blinded research staff members (including post-doctoral fellows, lab engineers, and research assistants) assist clinicians with training setup and clinical data collection. The study principal investigator oversees all study procedures and ensures the correct collection and documentation of data. If participants miss more than two walking practice sessions or intervention sessions, we will not conduct further assessments and exclude their data from analyses. However, if participants miss an assessment session, we record their data as “missing” at that time point.

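### The missed-session exclusion has no exception for safety stops, so an AD or hypertensive event that ends treatment early can remove itself from the Hypothesis 3 rates

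*Protocol article*

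**What the plan says.** All references are to the protocol article.

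- **Exclusion rule.** The last paragraph of Statistical analysis, directly after Hypothesis 3, states: "If participants miss more than two walking practice sessions or intervention sessions, we will not conduct further assessments and exclude their data from analyses". It makes no exception for the reason for absence and is not limited to particular aims. The only contrast drawn is that a missed assessment visit is recorded as missing.
- **Safety stops.** Protection against cardiopulmonary risk covers AD symptoms and continues: "rapid change in HR or systolic BP (SBP), diaphoresis, severe headache, or dizziness, participants will be withdrawn from the experiment". It then adds: "Return to the study requires medical clearance".
- **Rates.** The Blood pressure section divides hypertensive events by the number of readings, to account "for measurements not made because of dropout or a disqualifying adverse event". The section on AD incidence divides events by completed study days, to account "for days not measured because of dropout or a disqualifying adverse event".
- **Comparison.** Hypothesis 3 compares these rates by relative risk with a 95% confidence interval. It predicts no difference for tAIH versus placebo or for stimulation versus sham.
- **Cognition.** "We will assess cognitive function after the last walking practice session and after the last intervention session", that is, at T0 and T2. T2 is therefore the only cognitive measurement after treatment.
- **Adverse events.** Adverse event reporting separately records hypertension and AD for each participant through the end of follow-up.

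**The concern.** The event that Aim 3 counts can also cause the absence that triggers exclusion. A participant with AD during an intervention session is withdrawn. If clearance does not come, or comes late, more than two sessions are missed, and the rule removes the event and the days or readings already observed. The two rate definitions take the opposite course: they handle early loss by counting whatever was observed. Where the exclusion rule applies, both instructions cannot be followed.

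This matters because Hypothesis 3 is supported by finding no difference. If exclusions fall mainly in the two tAIH arms, the relative risk is pulled toward or below 1. If they fall equally on all arms, the ratio stays about the same and the interval widens. Both make the predicted result easier to obtain. The rule also stops further assessment, and data never collected cannot be recovered by a later analysis plan.

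**Working it through.** **1. When the rule applies.** Experiment protocol gives 8 walking practice and 8 combinatorial sessions. Counting the combinatorial sessions on their own, a stop in session k with no return and no make-up misses 8 − k sessions. This exceeds 2 for k = 1 to 5 (8 − 5 = 3; 8 − 6 = 2). If the interrupted session also counts as missed, it applies for k = 1 to 6. Sessions 7 and 8 never trigger it. If the chance of a first AD stop is assumed constant at 1% to 10% per session, 63% to 72% of such stops fall in sessions 1 to 5.

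**2. What is discarded.** The plan's session count reproduces: 16 sessions + 7 assessments (BL, T0, T1, T2, F1, F4, F8) = 23. Observed days at a stop:

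- session 1: 1 (BL) + 8 + 1 (T0) + 1 = 11
- session 5: 1 + 8 + 1 + 5 + 1 (T1) = 16

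Blood pressure is read every fifth breathing interval, so 15/5 = 3 readings per full breathing session. Up to 3 (session 1) to 15 (session 5) of these readings are lost, besides those from other visits.

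**3. What is not collected.** T2, F1, F4 and F8 are lost, which is 4 of 7 assessments. After a session 1 stop, sessions 2 to 4 are missed before T1, so 5 are lost.

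**4. Illustration with assumed counts.** The plan gives no AD rate to reproduce. Planned allocation is 20 per arm, so tAIH versus placebo is 40 versus 20. Assume 16 and 4 AD events and 23 days per completer. Rate ratio = (events/days in tAIH) / (events/days in placebo); the 95% interval multiplies and divides by exp(1.96 × √(1/a + 1/b)), where a and b are the event counts.

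All complete: (16/920)/(4/460) = 2.00 (0.67 to 5.98).

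Let m tAIH participants with one event each stop and not return:

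| m | Excluded | Kept with 11 to 16 observed days |
|---|---|---|
| 2 | (14/874)/(4/460) = 1.84 | 2.03 to 2.05 |
| 4 | (12/828)/(4/460) = 1.67 | 2.06 to 2.11 |
| 8 | (8/736)/(4/460) = 1.25 | 2.13 to 2.23 |

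For m = 8 kept: 16/(736 + 8 × 11) = 16/824 gives 2.23, and 16/(736 + 8 × 16) = 16/864 gives 2.13. The intervals for m = 8 are about 0.38 to 4.15 excluded, and 0.71 to 6.4 or 0.75 to 6.7 kept.

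Equal proportional loss (a quarter of events in each group, one per excluded participant): (12/828)/(3/437) = 2.11 (0.60 to 7.48). The ratio barely moves; the interval widens.

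**5. A second set of assumptions.** Take 20 per arm, 2 retained events in each of two arms, and 1 to 4 further combination-arm participants with one event each, stopped at day 14. The ratio is 1.53 to 3.25 if they are kept and 1.05 to 1.25 if excluded. For 4 participants: (6/424)/(2/460) = 3.25 against (2/368)/(2/460) = 1.25.

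**The case against.** The best defence is that the specific governs the general. The rate definitions deal with disqualifying adverse events by name, while the exclusion sentence sits in a paragraph about adherence and speaks of missing sessions, not of withdrawal. On that reading, withdrawn participants stay in the Aim 3 rates, and a separate analysis plan may say so. This reading is possible, but the article does not state it. The exclusion covers analyses without limit, and it also ends assessment, which an analysis plan cannot reverse.

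Several limits do stand:

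- A reader might infer that any AD event deletes itself. It does not: return after clearance is allowed, and brief or late stops fall outside the rule.
- A reader might infer that safety events disappear. They stay in the adverse event reports. What is lost is the between-arm comparison and the later visits.
- A reader might infer a known bias in favour of tAIH. AD stops can also occur in Placebo + WALK_tSTIM, and dizziness alone is not a Hypothesis 3 outcome, so excluding a dizzy participant need not remove an event.
- A reader might infer that the Aim 3 conclusion would change. In the illustrations the intervals include 1 whether participants are kept or excluded; only the estimate and its precision move. The case m = 8 is extreme, since it makes the whole planned 20% dropout of 40 consist of AD stops and excludes nobody on placebo.
- For those who never return, the withdrawal wording already ends participation, so the exclusion rule is not the sole cause of a missing T2.
- Missed walking practice does not bias the arms, because allocation follows completion of practice.

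**Conclusion.** The point holds in a conditional form. As written, the rule removes events and observed time from the Hypothesis 3 rates when an AD or hypertensive event leads to non-return after a stop in intervention sessions 1 to 5, or to a comparably long absence. That contradicts the stated purpose of both denominators, and it stops later assessments, including cognition at T2.

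The size and direction of bias cannot be computed, because the article gives no AD, hypertension or return rates by arm. The ratios above rest on invented counts and show only the mechanism. What can be said is that loss concentrated in the tAIH arms lowers the ratio and equal loss mainly widens the interval, and that both favour the prediction of no harm. The trigger range assumes no make-up sessions and a separate count for the intervention phase. The amendment is cheap and protects one of three aims, so it should be made.

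**What to change.** Amend the closing paragraph of Statistical analysis to say:

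- All allocated participants who received any intervention session are included in the Aim 3 analysis, with every event, blood pressure reading and study day observed up to withdrawal.
- Those who stop or miss intervention sessions are offered the remaining scheduled T and F assessments, if willing and medically cleared. Visits not attended are recorded as missing, as the paragraph already provides.
- The walking practice rule stays, since it acts before allocation.

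The cardiopulmonary section should say that withdrawal from treatment does not by itself end assessment. Its stopping triggers need no change.

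**Cost.** There are 4 to 5 extra visits per retained participant at $40 each, so $160 to $200. Planned non-completers are 60 − 48 = 12, giving at most 12 × $200 = $2,400 in visit payments, plus travel and staff time. Participants with a partial dose may also dilute the comparisons of pain, spasticity and cognitive scores.

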Daily tAIH priming enhances the potency of WALK_tSTIM_ on improving walking speed in people with chronic SCI. We quantify potency as the number of tAIH + WALK_tSTIM_ sessions (eight total) needed to achieve the MCID in walking speed.^57^ We assess walking speed with the 10MWT at the end of each training session and predict that those who receive tAIH + WALK_tSTIM_ will achieve an MCID with fewer training sessions than either treatment alone (Placebo + WALK_tSTIM_ or tAIH + WALK_tSHAM_). To test this hypothesis, we will use linear mixed models with number of sessions to achieve the MCID as the outcome with treatment group and 10MWT speed at baseline as fixed effects and participant as the random effect. We anticipate that improvement in walking recovery also will correlate with improved 6MWT, TUG, SCI-FAI, WISCI II, and LEMS scores, suggesting the clinical relevance of this intervention across impairment levels and walking deficits.

#### Hypothesis 3

Daily tAIH+WALK_tSTIM_ does not induce maladaptive changes (spasticity, pain, systemic hypertension, and AD) in persons with chronic SCI. We predict no difference in SCATS, NPRS, CVLT, O-TMT, NBDS, and NBSS scores after daily tAIH + WALK_tSTIM_ compared to baseline. We will use a Friedman two-way repeated-measures ANOVA by ranks to compare these relative scores between and within groups. Changes in these scores relative to baseline are the repeated measures. Intervention (tAIH + WALK_tSTIM_, Placebo + WALK_tSTIM_, and tAIH + WALK_tSHAM_) and time are the fixed main effects, with subject as the random effect. We also predict that tAIH + WALK_tSTIM_ will not elicit a greater incidence of systemic hypertension or AD in persons with chronic SCI.

To test these subhypotheses, we will compare the incidence rates of these maladaptive changes between interventions using the relative risk.^58,59^ A relative risk of 1 will indicate no association between the maladaptive measures and interventions. Using the 95% confidence interval of the relative risk,^59^ we will determine whether there is a statistically significant association between interventions. We predict that the relative risk of hypertension and AD are not different between tAIH versus placebo interventions and WALK_tSTIM_ versus WALK_tSHAM_ interventions.

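### The rule excluding anyone who misses more than two sessions makes no exception for the Hypothesis 3 safety analyses, although sessions can be lost because of harm

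*Protocol article*

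**What the plan says.** The exclusion rule stands at the end of the Statistical analysis section, after Hypotheses 1 to 3: "If participants miss more than two walking practice sessions or intervention sessions, we will not conduct further assessments and exclude their data from analyses". The sentence after it treats a missed assessment differently: only that time point is set to missing and the participant stays in.

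Hypothesis 3 in the same section is the safety hypothesis. For the scores it reads "We predict no difference in SCATS, NPRS, CVLT, O-TMT, NBDS, and NBSS scores" after the combination, relative to baseline. Hypertension and autonomic dysreflexia (AD) are compared between interventions by a relative risk with a 95% confidence interval.

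The section on protection against cardiopulmonary risk says how harm can cost sessions. On AD symptoms, rapid changes in heart rate or systolic pressure, severe headache or dizziness, "participants will be withdrawn from the experiment and provided skilled care from the research clinicians", and "Return to the study requires medical clearance". It also says: "If excessive discomfort or pain is reported, the intervention ends".

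Two outcome definitions assume something else about people who leave. The hypertension rate is built to account "for measurements not made because of dropout or a disqualifying adverse event", and the AD rate "for days not measured because of dropout or a disqualifying adverse event".

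The cognitive tests have only two time points: "We will assess cognitive function after the last walking practice session and after the last intervention session", that is T0 and T2.

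**The concern.** An adherence rule of this kind is familiar for a per-protocol efficacy set. Here it reaches the safety analyses, where the reason for missing sessions may be the outcome under study. A participant whose sessions stop because of AD symptoms, a blood pressure reaction or pain can pass the threshold and leave the comparison meant to detect that harm.

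Aim 3 hopes to show that the combination causes no harmful change. Removing the people who did worst favours that conclusion. With 20 planned per arm, a few removals could change the picture. A reader also cannot tell which text governs the hypertension and AD rates, so two analysts could obtain different relative risks from the same data.

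**Working it through.** The article gives no power or sample size for Hypothesis 3, so there is no stated figure to reproduce. The check is a comparison of rules, with a short count.

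**1. Can harm after assignment trigger the rule?** The Randomization section assigns groups in the order in which participants finish walking practice. Practice-phase losses therefore precede assignment and cannot be caused by the assigned treatment. Intervention-session losses follow assignment and can differ by arm. The cardiopulmonary section gives a harm route to such losses, and nothing says that sessions lost this way do not count as missed.

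**2. When does it bite?** Inputs: eight combination sessions, four per week (Experiment protocol); T1 at the end of week 3, so after session 4, and T2 at the end of week 4, so after session 8 (Figure 3 legend); threshold more than two missed. Assumptions: the participant stops for good after session k, sessions are not made up, and no missed practice session is added to the count.

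Missed by T2 = 8 − k, and exclusion follows if 8 − k > 2, so k ≤ 5. Missed by T1 = 4 − k for k < 4.

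| Last session k | Missed by T1 | Missed by T2 | Excluded | T1 score | T2 assessment |
|---|---|---|---|---|---|
| 1 | 3 | 7 | yes | barred | barred |
| 2 | 2 | 6 | yes | discarded if taken | barred |
| 3 | 1 | 5 | yes | discarded if taken | barred |
| 4 | 0 | 4 | yes | due after an attended session, then discarded | barred |
| 5 | 0 | 3 | yes | due after an attended session, then discarded | barred |
| 6 | 0 | 2 | no | kept | allowed |
| 7 | 0 | 1 | no | kept | allowed |

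Five of the seven early stopping points lead to exclusion. These are positions in the schedule, not probabilities; the count says nothing about how often participants stop there.

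**3. Which safety data are affected?**
- SCATS, NPRS, NBDS and NBSS: scores already held are removed, and later scores through the 8-week follow-up are not sought.
- CVLT3 and O-TMT: T2 is their only assessment after treatment. The article chose these tests because they cover the abilities most exposed to an excessive low-oxygen dose.
- Hypertension and AD rates: the definitions divide by measurements made or study days completed, so that short observation is allowed for. That adjustment serves its purpose only if people with short observation are in the data. The exclusion rule takes them out, and neither text says which prevails.

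**4. Direction.** The article gives no event rates. Purely as an illustration, assume participants with at least one AD event number 6 of 20 in the combination arm and 2 of 20 in a comparator:
- all kept: (6/20)/(2/20) = 3.00
- one of the six excluded: (5/19)/(2/20) = 2.63
- two excluded: (4/18)/(2/20) = 2.22
- three excluded: (3/17)/(2/20) = 1.76
- four excluded: (2/16)/(2/20) = 1.25
- instead, one of the comparator's two excluded: (6/20)/(1/19) = 5.70

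The between-arm ratio moves towards 1 when harm-related loss is concentrated in the combination arm, and away from 1 when it falls in the comparator. The within-arm comparison with baseline moves towards no change whenever those lost did worse. The planned rates are per blood pressure measurement and per study day, so these participant-level ratios show direction only.

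**The case against.** The best reply is that the hypertension and AD definitions are specific and the exclusion rule is general, and a specific rule normally governs. The harms named as grounds for withdrawal are largely the ones those two rates count, so the authors probably meant to keep these data. This is a fair reading of intent. It leaves a conflict to be resolved in writing, and the six score-based outcomes have no such provision.

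Second, being withdrawn on medical grounds is not plainly the same as missing a session, and the exclusion sentence sits in a paragraph about protocol adherence and data quality. Ending the intervention for pain may mean that session only. Nor does the article make a worse spasticity, bowel, bladder or cognitive score a reason to stop. These points stand: harm can lead to exclusion, but the document does not show that it must.

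Third, Adverse event reporting continues from enrolment to the last follow-up visit. So harm is not lost from the trial's whole safety record. Recording an event does not, however, return the participant to the Hypothesis 3 comparisons, and event reports do not replace the scheduled spasticity, bowel, bladder and cognitive scores.

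Some stronger readings are not supported:
- A reader might take the 20% dropout, 20 assigned against 16 completers per arm, as a ceiling of four affected per arm. It is a planning assumption. Actual losses may exceed it, fall unevenly, or have nothing to do with harm.
- A reader might blame the rule for every absent T2 cognitive score. Someone who stops for good may not return anyway; the rule's own effect is on those who resume or would still attend.
- A reader might suppose that waiting for medical clearance will by itself pass the threshold. The article gives no clearance time.

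**Conclusion.** The point holds as a defect in a stated rule. As written, the exclusion applies to Hypothesis 3, can remove participants because of harm suffered after assignment, discards safety scores already collected, and bars later ones from willing participants. It is also inconsistent with the hypertension and AD denominators.

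The resulting bias can favour a finding of no harmful change. Its size is unknown and may be zero. It depends on how many participants lose more than two intervention sessions through harm, on the arms they are in, and on whether medically lost sessions are counted as missed. The conclusion rests on the plain reading that the word analyses includes those of Hypothesis 3. The rule should be corrected before the data are analysed; the point does not call the efficacy design into question.

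**What to change.** Add one statement to the Statistical analysis section: the exclusion for missed sessions does not apply to Hypothesis 3. Then specify three things.

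1. Every participant who received at least one assigned intervention session (tAIH or placebo, stimulation or sham) enters all Hypothesis 3 analyses, including the cognitive tests.
2. The hypertension and AD rates use all observed measurements and all completed study days of these participants. This settles the conflict with the outcome definitions.
3. Safety assessments already on the schedule continue after missed sessions or a stopped intervention, where the participant agrees.

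The cost is wording and a few more of the visits already planned. The downside is that some partly treated participants enter the safety comparison, which dilutes exposure slightly. The analysis sets for Hypotheses 1 and 2, the enrolment of 60 and the stated power are unchanged.
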